### 1628 5.4 Demographic Variables

1629 **For first parent:** Relationship to child – parent, adoptive parent, foster parent, step parent, grandparent, sibling,  
1630 other

1631 **For both parents/ care-givers:**

1632 Parent age

1633 Parent gender

1634 Parent ethnicity

1635 Relationship status –married/remarried/civil partnership, single (never married, never in civil partnership),  
1636 cohabiting, divorced (including separated civil partnership, including legally separated), widowed (including  
1637 from civil partnership)

1638 Highest qualifications (no GSCE's, GCSEs or equivalent, College (A-levels, NVQ or BTEC), undergraduate,  
1639 postgraduate.

1640 Employment status – full time, part time, paid parental leave, student, no paid job.

1641 Whether or not it is their first child  
1642 Number and ages of their other children if not first child.

1643

## 1644 **Child demographics**

1645 Age at randomisation

1646 Gender

1647 Ethnicity

1648 Birth weight

1649 Breast feeding attempted or not

1650 Number of months exclusively breast fed

1651

## 1652 **6 Statistical Methodology**

### 1653 **6.1 General Methodology**

1654 **Descriptive data:** Continuous/ numeric variables that follow an approximately Normal distribution will be  
1655 summarised using the mean and standard deviations. Skewed variables will be summarised using the median  
1656 and inter-quartile range. Categorical variables (binary and ordinal and multinomial) will be presented as  
1657 frequencies and percentages. Scores from psychometric scales will be treated as numeric.

1658

1659 **Statistical models to be used for obtaining estimates of the treatment effect on child behaviour outcomes:**  
1660 These statistical models will have either PPACS score or CBCL score or SDQ at follow-up (based on  
1661 assessment by the primary or secondary -care giver) as the outcome, and will be adjusted by baseline  
1662 measurements of the same score, time from randomisation to follow-up assessment, recruitment centre, age of  
1663 child at recruitment and parental involvement (one or two parents/ care-givers) as fixed effects. SDQ measured  
1664 by a teacher/ some-one external to the family, will be adjusted for primary care-giver SDQ at baseline.

1665  Adjusting for centre as a random effect, although planned in the protocol, will not be statistically robust owing  
1666 to there being only a very small number of centres. As an alternative, centre has been included as a fixed effect  
1667 in the proposed model.

1668

1669 **Checking of assumptions underlying hypothesis tests and models:** Histograms and box-plots will be used to  
1670 assess the distributional assumptions required for the models that will be fitted and to check for possible  
1671 outliers. Log transformations will be applied, where appropriate, in order to render outcomes variable  
1672 distributions closer to the Normal. If neither the variable itself nor its log result in residuals from the regression  
1673 analysis that are close enough to the Normal distribution to allow regression results to be reported confidently,  
1674 then boot-strap techniques will be undertaken to calculate confidence intervals, after relaxing the assumptions of  
1675 normality. The relationship between the outcomes and other variables will be explored graphically, using scatter  
1676 plots and box-plots.

1677 **Statistical significance level:** Results will be interpreted according to a 5% significance level.

1678 **Missing data on primary outcome measure (PPACS):** Before starting the data analysis, the level, pattern and  
1679 likely causes of the missingness in the baseline variables and outcomes will be investigated by forming  
1680 appropriate tables. This information will be used to determine whether the level and type of missing data has the  
1681 potential to introduce bias into the analysis of the PPACS results.

1682 **Missing data on individual questions which make up measurement scales:**

1683 For our care-giver outcome variables, we will use the manuals on each questionnaire to determine the  
1684 appropriate treatment of missing data items. When there is no information on this in the manuals, then we will  
1685 replace the missing values with single imputed values with a random residual, based on responses to other items  
1686 on the same subscale of the questionnaire, provided not more than 20% of the questions within the questionnaire

or 33% of the questions within a subscale (for questionnaires other than the PPACS) are missing for that person. Otherwise, we will consider that outcome variable summary score to be missing for that person.

There is no information on treatment of missing values in the manuals for PPACS, our primary outcome measure. For PPACS, CBCL and SDQ (our child behaviour outcomes) a multiple imputation will be used on the individual questions within each questionnaire at baseline and at follow-up, in order to optimise our treatment of missing data. These multiple imputation analyses will be the primary analyses for these outcomes. Any child who has a PPACS at follow-up with at least 50% of the questions completed will be included in this multiple imputation PPACS outcome analysis. We will base our imputation on completed questions and subscale scores from the PPACS questionnaire at outcome and total scores at earlier time points. For multiple imputation at baseline, we will base our imputation on completed questions and subscale scores from within the PPACS questionnaire at baseline only. The methods will be the same for CBCL and for SDQ. These multiple imputation models can be difficult to fit, and sometimes it is not feasible to come up with a solution. If this proves to be the case, after trying a number of different strategies aiming to get a solution, or if there is reason to believe that assumptions are violated to the extent that any solution is not statistically robust, then we will use a simpler method of dealing with missing. The simpler method is to scale up psychometric scores to account for missing responses on individual items that make up the scale. The sum of non-missing items is scaled up, according to the proportion of the maximum total scale score derives from non-missing items. If there are fewer than 10% of the patients who have 10% or more of their questions missing within the specified questionnaires, then the simpler strategy may be used in any case, since it will produce virtually identical results.

**Changes from official signed draft:** The paragraph on “statistical modelling to be used on obtaining estimates of child behaviour outcomes” was moved to improve the overall flow. This was moved from toward the end of this section to become the second paragraph of this section. Missing outcomes of care-giver outcomes will now generally be dealt with by single imputation with a random residual. For PPACS, the text previously read “Any child who has a PPACS at follow-up with at least 80% of the questions completed will be included in this multiple imputation PPACS outcome analysis (and if a number have fewer than 80% complete, we may revise this threshold downwards).” Because there is indeed some missing data at baseline, because not all questions were relevant to younger children, the 80% threshold has been revised downwards to 50%. The multiple imputation for missing items within PPACS will now be based on individual items and subscale totals, rather than solely on individual items, so that there will generally be some residual variation in the imputation models. The most fundamental change to the PPACS multiple imputation is detailed in section 6.2 primary efficacy analysis below. The simpler strategy for dealing with missing data was clarified; this may be used if there is little missing data or if multiple imputation fails.

**Change from SAP version 1.0:** We now adjust all key outcome analyses (primary and secondary outcomes on child behaviour and on parental well-being, including their subscales) for time from randomisation to follow-up assessment.

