### 1502 3.6 Sample Size

1503 The total sample size will be 300 participants.

1504 If losses to follow-up are 20%, this leaves 120 participants per group with follow-up data. We would then have  
1505 80% and 90% power to detect standardised effect sizes of 0.36 and 0.42 respectively, at the 5% significance  
1506 level, using an independent samples t-test. In addition, we have stated that our analysis will adjust for baseline  
1507 behavioural score, research centre and age of child, and parental involvement (one versus two) which will  
1508 increase power, probably to over 90% for the 0.36 effect size (since such adjustment will reduce the residual  
1509 error variance in our model). Kahan and colleagues (2014, ref 1) found that covariate adjustment for 1 to 4  
1510 variables in trials increased power from 80% to a median of 93% power in their sample of 12 outcomes assessed  
1511 across 8 studies.)

1512 We have conservatively allowed for a potential drop-out rate of 20% because of the longer follow-up time in the  
1513 proposed study, even though previous intervention studies detailed below have maintained retention rates of  
1514 over 90% at follow-up.

1515 The pooled effect size for all randomised controlled trials to date that have used the same video feedback  
1516 intervention (ViPP) is 0.46 ([name], 2013, personal correspondence). Other relevant literature  
1517 for interventions for behavioural problems, predominantly in slightly older children, yield higher effect size  
1518 estimates. In the systematic reviews undertaken for the most recent NICE guidance on conduct disorders in  
1519 children and young people (ref 2), the pooled effects for parent-focussed interventions yielded estimated effect  
1520 sizes of 0.69 standard deviations for researcher-rated outcome (the main outcome measure in the proposed  
1521 study), and 0.54 for parent-rated outcome. In a study of the Incredible Years programme in 2-9 year olds (ref 3)  
1522 effect sizes ranged from 0.48-0.78. In the SPOKES trial (ref 4) of intervention for parents of 6 year olds, the  
1523 effect size for behavioural outcomes was 0.52 SD difference between the treatment and control group. Where  
1524 parenting programmes have been rolled out across the UK (ref 5-6) similar effect sizes have been found, albeit  
1525 in non-randomised designs (effect sizes ranged from 0.44-0.71).

1526

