### 3.10 Randomisation

Randomisation lists were prepared by a statistician independent of the trial ([name]) using computer generated 1:1 allocation (ViPP intervention vs treatment as usual) and variable block sizes. Randomisation will be stratified by treatment centre and by number of parents/ care-givers participating (one or two). The randomisation lists (one for each strata) will be uploaded on to InForm (the study electronic data capture system) and eligible subjects allocated online to the next available treatment code in the appropriate randomisation list.

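### SAP 6.1 imputes missing follow-up PPACS items without randomised group or child age, which SAP 6.2 does use; this biases the treatment effect, usually toward zero, by an amount the documents do not allow one to fix

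*Combined protocol and SAP*

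**What the plan says.** SAP 6.1 makes multiple imputation of individual items the primary approach for PPACS, CBCL and SDQ. For PPACS items at follow-up the stated predictors are: "We will base our imputation on completed questions and subscale scores from the PPACS questionnaire at outcome and total scores at earlier time points". For baseline items, "we will base our imputation on completed questions and subscale scores from within the PPACS questionnaire at baseline only". Neither list names randomised group or child age. The method is said to be the same for CBCL and SDQ.

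Item-level imputation at follow-up applies to "Any child who has a PPACS at follow-up with at least 50% of the questions completed". The threshold was lowered from 80% to 50%. The reason given is that some baseline items were missing "because not all questions were relevant to younger children".

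SAP 6.2 covers children whose PPACS is wholly missing or below the threshold. Their 5-month outcome is imputed from randomised group, sex, age at that assessment and baseline PPACS, CBCL and SDQ scores. The analysis model in SAP 6.1 adjusts for baseline score, time from randomisation to assessment, centre, age at recruitment and one versus two caregivers.

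**The concern.** An imputation model should contain at least the variables of the analysis model, and above all the treatment indicator when the outcome is being imputed. Without it, missing items are predicted as if both arms followed one common relation, so only part of any treatment effect reaches the imputed items.

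The two sections are also inconsistent. A child with 49% of items answered is imputed with arm and age in the model; a child with 51% answered is imputed with neither. No reason is given. Age is moreover the SAP's own explanation for missing items, so the variable said to drive missingness is outside the model.

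At stake is the primary outcome. The short-term cost-effectiveness analysis in SAP 7.3 relies on the item-level imputation alone. The subgroup plot in SAP 10.3 splits children at 24 months of age, so if the younger group has more imputed items, any dilution would concentrate there.

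**Working it through.** **The plan's own figure.** SAP 3.6 states "If losses to follow-up are 20%, this leaves 120 participants per group with follow-up data", with "80% and 90% power to detect standardised effect sizes of 0.36 and 0.42 respectively, at the 5% significance" "level, using an independent samples t-test". The expected test statistic is d × √(120/2) = 7.746d. For d = 0.36 it is 2.789, and power = Φ(2.789 − 1.960) = 79.6%. For d = 0.42 it is 3.253, and power = Φ(1.293) = 90.2%. The noncentral t gives 79.3% and 90.0%. Also 120/0.8 = 150 per arm. The stated power reproduces. The documents give no figure for the imputation, so the rest is a scenario range.

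**Assumptions not in the documents.** 20 exchangeable items; inter-item correlation ρ of 0.1 to 0.3; a share p = 0.5 of children (those under 24 months) missing the same fraction f = 10%, 20% or 50% of follow-up items; true effect 0.36 SD; latent correlation 0.7 between baseline and follow-up.

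**Closed form, effect even over items.** An item imputed without arm from m answered items carries a fraction b = mρ/(1 + (m−1)ρ) of the effect. The trial-level loss is p × f × (1 − b).

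- f = 0.5, ρ = 0.1 (m = 10): b = 1/1.9 = 0.526; loss = 0.25 × 0.474 = 12%.
- f = 0.1, ρ = 0.3 (m = 18): b = 5.4/6.1 = 0.885; loss = 0.05 × 0.115 = 0.6%.

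The baseline total is also a listed predictor and carries no treatment effect, so it takes weight away from the answered items. With v = ρ + (1−ρ)/m, w = ρ + (1−ρ)/20 and c = 0.7ρ, the fraction becomes b′ = (ρw − c²)/(vw − c²). For f = 0.5 and ρ = 0.1: v = 0.19, w = 0.145, c = 0.07, so b′ = 0.0096/0.02265 = 0.424 and the loss is 0.25 × 0.576 = 14%.

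**Simulation.** 120 per arm, proper multiple imputation with Rubin's rules, then regression on arm, baseline and age. Each cell gives the estimate without arm and age / with both.

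| Items missing in half the children | ρ = 0.1 | ρ = 0.2 | ρ = 0.3 |
|---|---|---|---|
| 10% | 0.354 / 0.361 | 0.360 / 0.365 | 0.359 / 0.363 |
| 20% | 0.343 / 0.359 | 0.350 / 0.360 | 0.353 / 0.360 |
| 50% | 0.307 / 0.359 | 0.324 / 0.359 | 0.331 / 0.356 |

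Against complete data in the same runs, the loss is about 1% (0.359 against 0.363) to 5% (0.343 against 0.360) in the first two rows. In the worst cell it is about 15% (0.307 against 0.359), with power 71% against 78% when arm and age are included.

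**Direction.** If the whole effect lies in the items the younger children do not answer, the estimate without arm roughly halves, to 0.17-0.19. If it lies only in the answered items, the estimate rises to 0.37-0.47, so the arms move apart.

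**Age.** With an assumed slope of 0.5 item SD per 12 months, imputed items in the younger children came out about 0.5 item SD too high.

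**The case against.** Age-driven missingness is documented at baseline only, and baseline values precede treatment, so leaving arm out of that model cannot dilute the effect. This stands. The arm point concerns outcome items, where age-driven missingness is an inference. It is a reasonable one: the SAP uses the baseline observation to lower the follow-up threshold, and children who enter at 12-36 months are about 17-41 months old at the 5-month visit, which overlaps the entry range.

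A reader might infer that the plan is bound to pull the arms together. The documents do not support that, because the direction depends on which items carry the effect. A reader might also infer that omitting age biases the primary comparison. That does not follow: age is balanced by randomisation and is an analysis covariate, and an imputed value also draws on the child's own other answers. The main consequence is a shift in score levels.

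The plan has other provisions. Missingness is to be tabulated first. Simple scaling-up of answered items replaces imputation if imputation fails or its assumptions look violated, and may be used if fewer than 10% of patients miss 10% or more of items. Imputed items are to be shifted by one point each way, and one analysis keeps only PPACS at least 80% complete. These limit the problem when little is missing, but none of the sensitivity analyses puts arm into the item model: the shift is the same in both arms, the 80% rule only drops children, and SAP 10.2 applies the primary item imputation to every analysis in the forest plot.

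The predictor lists may not be meant as exhaustive, but nothing in the text says that arm or age is added.

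**Conclusion.** The point holds in a limited form. Followed as written, SAP 6.1 imputes outcome items under a model without arm, contrary to SAP 6.2 and to the analysis model. The resulting bias is usually toward zero. With an effect even over items it is about 1-5% when half the children miss 10-20% of items, and up to about 15% when they miss half. This rests on the assumed 20 items and correlations of 0.1-0.3. The true size depends on item-missing rates that the documents do not report, and it may be small. The reverse direction is possible. The halving seen when the whole effect sits in unanswered items is a bounding case that nothing in the documents supports. Omitting age is a matter of score levels in the youngest children rather than of the overall arm contrast.

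**What to change.** In SAP 6.1, add randomised group, age at assessment and the remaining analysis-model covariates (centre, time to follow-up, number of caregivers) to the follow-up item-level models for PPACS, CBCL and SDQ, in line with SAP 6.2. Age at assessment is age at randomisation plus follow-up time, so any two of these three suffice. Add child age to the baseline item model; arm is not needed there. Earlier total scores are already listed and need no change. Report the share of items imputed by arm and age band.

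Adding age does not settle the case of an item never asked below a certain age, since any imputed value is then an extrapolation. If the data allow such items to be identified, add a sensitivity analysis that does not impute them, and state how the total is then formed. The documents do not show that a separate code for inapplicable items was recorded. SAP version 2.0 is dated May 2019 and recruitment ended in July 2017, so this part depends on what the records already contain.

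The cost of the main change is a few lines of SAP text and added predictors that the analysis model already requires.

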## 6.2 Primary Efficacy Analysis

The primary endpoint, externalizing behaviour (PPACS), will be analysed at follow-up, using the regression model suggested above, with multiple imputation of individual missing questions within the PPACS questionnaire, as described under treatment of missing values. This approach will maximise the power, by including baseline scores into the regression analysis. It will also ensure the most appropriate and unbiased treatment of anyone who has missing data on any item within the PPACS questionnaire. The primary analysis will also incorporate multiple imputation for anyone whose PPACS at outcome is completely missing (or with fewer items completed than the threshold). At 5 months follow-up, these will be imputed based on randomised group, gender of child, age of child at 5 month assessment, baseline PPACS, CBCL and SDQ scores. At 2 year follow-up, these will be imputed based on randomised group, gender of child, age of child at 2 year assessment, and PPACS, CBCL and SDQ scores (at 5 month follow-up, if available or else using these PPACS, CBCL and SDQ scores at baseline).

Sensitivity analyses will firstly be a complete case analysis (with multiple imputation solely of missing items within PPACS). We will perform further sensitivity analyses by assuming firstly that completely missing PPACS scores are one SDC lower (than anticipated by multiple imputation), and secondly by assuming that they are one SDC higher (than anticipated by multiple imputation) (truncated to maximum and minimum possible scores on PPACS). [SDC represents one standard deviation of changes in PPACS where changes are

calculated as PPACS at f/u minus PPACS at baseline]. There will be further sensitivity analysis, based on those with missing items within the PPACS questionnaire. They are filled in initially on a missing at random assumption, and then by assuming that they are one point higher on each item than MI prediction, and then one point lower (truncated to maximum and minimum possible scores on each item).

Additional sensitivity analysis will be added to take account of our original analysis plan, which did not incorporate adjustment for length of follow-up (from randomisation to measurement of outcome). Lack of adjustment for this length of follow-up will be combined with the different assumptions about missing values, including on the complier average causal effects model and final model listed below. The complier average causal effects model also has a sensitivity analysis noted on it. This sensitivity (without adjustment for length of follow-up) will be applied to total scores on PPACS, SDQ (primary and secondary care-giver assessment) and CBCL (primary and secondary care-giver assessment).

An additional sensitivity analysis on the PPACS will only include PPACS measurements when they have at least 80% of questions completed. Anyone without PPACS measurements at follow-up (on this basis) will be excluded from the analysis (since this is the analysis method that was written into our official signed draft).

**Changes and additions from official signed draft:** The primary efficacy analyses now include multiple imputation of outcomes, for people whose PPACS is completely missing at follow-up. The original analysis is now listed as a sensitivity analysis. Other sensitivity analyses have been added. The technical aside was removed from this section since it is not relevant to analysis as presented here.

**Changes from SAP 1:** Sensitivity analyses and primary analyses have been reversed, in respect of adjustment for length of follow-up. This adjustment is now incorporated into the main analyses (of both 5 month and of 24 month outcomes). Lack of such adjustment is now incorporated into sensitivity analyses.

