769 using scatter plots and box-plots. Continuous variables that follow an approximately Normal distribution will be

770 summarised using the mean and standard deviations. Skewed variables will be summarised using the median

771 and inter-quartile range. Categorical variables (binary and ordinal and multinomial) will be presented in terms of

772 frequencies and percentages.

773 Before starting the data analysis, the level, pattern and likely causes of the missingness in the baseline variables

774 and outcomes will be investigated by forming appropriate tables. This information will be used to determine

whether the level and type of missing data has the potential to introduce bias into the analysis results or reduce substantially the precision of estimates for the proposed statistical methods. The primary outcome, externalizing behaviour (Pre-PACS), will be analysed at follow-up using linear regression analysis (after checking regression assumptions), adjusting for treatment centre, parental willingness to participate (one or two parents), for infant's baseline behaviour and for infant's age at randomisation. Sensitivity analyses will be undertaken, based on assuming that missing outcomes are the worst possible, or the best possible, in different randomisation groups. If these show that conclusions may differ based on missing values, then supplementary multiple imputation for missing values will be undertaken. These analyses will account for results of any losses to follow-up insofar as they pertain to differences in measured variables (i.e. under the assumption of missing at random). This will enable us to effectively incorporate information gleaned from earlier follow-up times when the final follow-up outcome is absent. This will be done by incorporating outcomes at earlier time points into the predictive model for the multiple imputation of the outcome at 2 year follow-up. Secondary outcome variables will be analysed similarly.

Categorical outcome variables will be presented by treatment group, and compared using logistic/ ordered logistic regression adjusted as per linear regression above.

A detailed statistical analysis plan will be prepared and signed off prior to any interim analyses.

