## 1548 4 Randomised populations

### 1549 4.1 Intent-to-Treat Population

1550 The primary analysis will be conducted using intention to treat approach. A substantial effort will be made to  
1551 obtain follow-up data on all participants (unless they drop out of the study and withdraw their consent to our  
1552 following them up). Baseline data will be analysed on all patients, unless they withdraw consent for this data to  
1553 be used.

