### 6.3 Complier average causal effects analysis

This will be performed by two stage least squares regression analysis on **PPACS**. The definitions for compliers and non-compliers/treatment not received is given in 4.3. As is standard practice for CACE analysis, it is assumed that there is no effect of being randomized to a particular group, other than the effect that results from receiving the intervention in practice (with at least 4 visits).

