**Parental/ care-giver Sensitivity\***

Baseline

5 month follow-up

24 month follow-up

Treatment effect is the difference in mean between treatment groups from regression analysis of the outcome measure on the baseline score of that same measurement, on treatment centre, on randomised group, on length of follow-up, on age of child and on number of parents/ care-givers participating (all treated as fixed effects).

Where any child has two male or two female care-givers, their scores will be averaged prior to inclusion in the above analysis, to avoid violating the assumption of independence.

**Changes from official signed draft:** AUDIT assessment of alcohol consumption has been removed from this table.

1941  
1942

8.13 Table: Attendance at Sessions and Satisfaction with Treatment amongst those allocated to the ViPP group

|                                                                                                   | One parent/ care-giver
agreed to participate

n (%) | Two parents/ care-givers agreed to
participate |                     |
|---------------------------------------------------------------------------------------------------|--------------------------------------------------------------|---------------------------------------------------|---------------------|
|                                                                                                   |                                                              | First

n (%)                                | Second

n (%) |
| Attended all sessions                                                                             |                                                              |                                                   |                     |
| Number of session attended                                                                        |                                                              |                                                   |                     |
|                                                                                                   | 5                                                            |                                                   |                     |

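### Sessions received is missing from the primary imputation model (SAP 6.2), so the ITT estimate may lean towards benefit if early stoppers are lost more often, and no analysis in the SAP tests this

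*Combined protocol and SAP*

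**What the plan says.** SAP 4.1 sets the estimand: "The primary analysis will be conducted using intention to treat approach". SAP 6.2 then states: "The primary analysis will also incorporate multiple imputation for anyone whose PPACS at outcome is completely missing", and treats a PPACS below the item threshold in the same way. The predictors are listed: "At 5 months follow-up, these will be imputed based on randomised group, gender of child", followed by age at the assessment and baseline PPACS, CBCL and SDQ. The 24-month list is of the same kind, with 5-month scores where they exist and baseline scores otherwise. SAP 6.4 carries the same treatment over to CBCL and SDQ. Neither list contains sessions received.

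Attendance is recorded. Table 8.13 has a block headed "Number of session attended" for the ViPP arm, and SAP 4.3 counts a family as having received the intervention if it attended at least four of the six visits. For the complier analysis, SAP 6.3 assumes no effect of randomisation "other than the effect that results from" actually receiving ViPP, again with at least four visits.

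For wholly missing scores, the checks in SAP 6.2 are a complete-case analysis and two shifts. The first assumes that "completely missing PPACS scores are one SDC lower (than anticipated by multiple imputation"; the second moves them one SDC higher. Neither shift is stated by arm. Protocol 13.2 had planned something different: "Sensitivity analyses will be undertaken, based on assuming that missing outcomes are the worst possible, or the best possible, in different randomisation groups". SAP 6.2 does not repeat that analysis.

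**The concern.** Protocol 13.2 justifies multiple imputation on the ground that loss can be explained by measured variables, that is, missing at random. In the ViPP arm, the number of sessions a family took is an obvious measured candidate for predicting both loss and outcome. With it left out, two ViPP families with the same sex, age and baseline scores get the same predicted outcome whether they took six sessions or none. The prediction comes from ViPP families seen at follow-up. If stoppers are lost more often, attenders are over-represented among these.

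Under intention to treat, a family that gave up ViPP should count with the outcome of a family that gave it up. If stoppers are lost more often and do worse given baseline, the primary estimate moves from the ITT effect towards the effect in attenders. Such a bias does not show in the confidence interval. The complete-case analysis has the same expectation, so its agreement with the imputed result would be no reassurance.

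**Working it through.** **Inputs.** From the plan: 150 per arm (SAP 3.3); 20% loss and an effect of 0.36 SD (SAP 3.6); the cut at four sessions (SAP 4.3). Assumed, because the documents give no values: the share of ViPP families that stop early, the share of those lost, and the effect in stoppers. Loss is taken as equal in the two arms and, among controls, as unrelated to outcome given baseline.

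**The plan's own figure.** With 120 per arm and a two-sided 5% test (sidedness is not stated), power is Φ(0.36×√60 − 1.96) = Φ(0.83) = 79.6% and Φ(0.42×√60 − 1.96) = Φ(1.29) = 90.2% (79.3% and 90.0% by the t-test). The stated 80% and 90% reproduce. The plan gives no figure for the effect of missing data on the estimate.

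**Formula.** Let q be the share of ViPP families attending 4-6 sessions, m the ViPP loss, m_c the loss among attenders, and D the effect in attenders minus that in stoppers. Among families seen, the attender share is q_obs = q(1 − m_c)/(1 − m). Imputation without sessions reproduces that mix, so bias = D × (q_obs − q). If stoppers get no benefit, the relative bias is (1 − m_c)/(1 − m) − 1.

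**At 20% loss, with 0.36 SD in attenders and 0 in stoppers:**

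| Stop early | Of these, lost | Attenders lost | True ITT | Plan's imputation | Bias |
|---|---|---|---|---|---|
| 20% | 60% | 10.0% | 0.288 | 0.324 | 0.900/0.80: +12.5% |
| 10% | 60% | 15.6% | 0.324 | 0.342 | 0.844/0.80: +5.6% |
| 20% | 40% | 15.0% | 0.288 | 0.306 | 0.850/0.80: +6.25% |
| 30% | 50% | 7.1% | 0.252 | 0.293 | 0.929/0.80: +16% |

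**At 10% loss**, halving every loss rate in the table gives 0.950/0.90, 0.922/0.90, 0.925/0.90 and 0.964/0.90, that is +5.6%, +2.5%, +2.8% and +7.1%. The ceiling, with every lost ViPP family a stopper without benefit, is 1/0.80 (+25%) at 20% loss and 1/0.90 (+11%) at 10%.

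**Other assumptions about stoppers** (20% stop, 20% loss, half of stoppers lost, true ITT 0.36). Here m_c = 0.10/0.80 = 0.125, so q_obs = 0.80×0.875/0.80 = 0.875 and q_obs − q = 0.075.
- No benefit: D = 0.36/0.80 = 0.45, bias +0.034 (+9%).
- Half the benefit: D = 0.40 − 0.20 = 0.20, bias +0.015 (+4%).
- Stoppers 0.3 SD better: bias −0.022.
- Loss unrelated to stopping: q_obs = q, bias 0.

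**Simulation** (150 per arm, true ITT 0.36, 20% stop early, baseline correlation 0.5, 10 imputations, 1,000 trials; no benefit in stoppers except in the last row):

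| Scenario | Plan | Sessions added | Plan, +1 SDC both arms | Plan, +1 SDC ViPP only |
|---|---|---|---|---|
| 20% loss, unrelated to stopping | 0.359 | 0.358 | 0.359 | 0.156 |
| 20% loss, half of stoppers lost | 0.391 | 0.357 | 0.391 | 0.186 |
| 20% loss, 80% of stoppers lost | 0.429 | 0.363 | 0.430 | 0.224 |
| 10% loss, 40% of stoppers lost | 0.393 | 0.362 | 0.392 | 0.289 |
| 20% loss, half of stoppers lost, half benefit | 0.375 | 0.360 | 0.377 | 0.172 |

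The shift columns follow from simple arithmetic. Moving all missing scores by one SDC changes the difference by SDC × (loss in ViPP − loss in control), which is zero when losses are equal. Moving the ViPP arm alone changes it by SDC × 0.20. At correlation 0.5 the SDC is √(2×0.5) = 1 SD, so 0.391 becomes about 0.19.

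**Precision.** In a separate simulation of the first row of the first table (3,000 trials, 5 imputations), the estimate was 0.324 without sessions and 0.290 with them, against a truth of 0.288. The empirical standard error rose from 0.114 to 0.118.

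**The case against.** The documents do not say how many families stop early, how many of those are lost, or how they fare. SAP 4.1 commits to a substantial effort to follow every family that has not withdrawn consent to follow-up, and SAP 3.6 calls 20% loss conservative and cites retention above 90% in earlier studies. A reader might infer that the primary estimate is overstated. The documents do not support that: it needs stoppers both to be lost more often and to do worse given baseline, and neither is reported.

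Three other stronger readings also fail.
- Lost stoppers are not given the average ViPP-arm result. Their values depend on sex, age and baseline scores, and the families that inform the model include stoppers who were seen.
- SAP 6.3 does not oblige the primary analysis to impute stoppers with no benefit. It states a standard assumption for a secondary analysis, and stoppers need not share the prognosis of controls with the same baseline.
- The problem is not equal at both visits. At 24 months a stopper seen at 5 months brings its own 5-month scores into the imputation.

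The gain in total error is also small. A bias of 0.036 is about a third of the standard error of 0.114. In 2,500 simulated trials, root mean squared error for the plan against the fix was 0.120 v 0.118, 0.117 v 0.117, 0.113 v 0.114 and 0.124 v 0.119 in the four rows of the first table. With half the benefit in stoppers in the first row, the fix did worse (0.117 v 0.121). Few stoppers would be observed: 150×0.20×0.40 = 12 in the first row and 150×0.10×0.40 = 6 in the second. They may differ from those lost, so the fix still rests on missing at random.

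All of this stands, and it limits the claim to a possible bias of modest size. It does not explain leaving out a recorded variable, nor does it supply a check. Protocol 13.2 would have provided an arm-specific one, but SAP 6.2 sets out its own list without it, and the forest plot in SAP 10.2 is tied to that list.

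**Conclusion.** The point holds as a risk of bias, not as a demonstrated one. The primary imputation omits a recorded post-randomisation variable that is likely to predict loss and outcome in the ViPP arm. The most plausible direction is towards benefit. At 20% loss, with no benefit in stoppers and stoppers over-represented among the lost, the four assumed cases give +5.6% to +16%; the same cases at 10% loss give +2.5% to +7.1%. The bias is roughly halved or less if stoppers keep half the benefit, absent if loss is unrelated to stopping or outcomes do not differ given baseline, and reversed if stoppers do better, for example because they stopped when the child improved. Where 5-month scores exist, the 24-month analysis is partly protected. The same reasoning applies to CBCL and SDQ through SAP 6.4.

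The firmest part does not depend on the size of the bias: as written, the SAP's checks on wholly missing PPACS would not show the problem if it were present.

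**What to change.** 1. In SAP 6.2, in the imputation models for wholly missing PPACS (and for CBCL and SDQ through SAP 6.4), replace randomised group with three levels: control; ViPP with 0-3 sessions; ViPP with 4-6 sessions. Use the family-level count of SAP 4.3. Count sessions completed before the assessment or, where there was none, before the end of its window. SAP 4.3 counts up to the assessment only, so the second half of that rule is new and needs to be written down.

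2. Leave the analysis regression on randomised group alone, so that it remains an ITT analysis.

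3. Apply the one-SDC shifts to one arm at a time, in line with the intent of protocol 13.2, and include the results in the forest plot of SAP 10.2. If nearly all stoppers are lost, the three-level term is only weakly identified and these shifts become the main safeguard.

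The cost is a few sentences of SAP wording and no new data. The standard error rises by about 1-4% in the scenarios run (0.114 to 0.118 in the first), and total error hardly changes. If stopping has no bearing on loss, the estimate stays where it was (0.36 either way in simulation).
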